### Study Sample

Eligibility criteria, screening, and consent are the same for the R21 and R33 phases. All participants will be transgender women who are eligible based upon inclusion criteria consistent with US Centers for Disease Control and Prevention and Thailand Ministry of Public Health PrEP guidelines [52,53]: (1) age 18 to 29 years; (2) male sex at birth; (3) self-identification as a woman or transgender woman or cultural identification with the female spectrum; (4) laboratory-confirmed HIV negative status; (4) self-reported recent history of condomless sex; (5) ability to understand, read, and speak Thai; and (6) either no existing use of PrEP (group 1, PrEP naive) or currently on PrEP but not adherent (taking ≤3 pills/week) in the past month (group 2, PrEP users). The exclusion criteria are (1) a serious cognitive or psychiatric problem compromising the ability to provide informed consent; (2) active suicidal ideation or major mental illness (eg, untreated psychosis or mania) at the time of the interview (these patients will be referred for treatment); (3) laboratory or clinical findings that would preclude PrEP initiation (eg, decreased creatinine clearance); and (4) current enrollment in another HIV intervention study. We will recruit transgender women from a broad range of socioeconomic backgrounds; therefore, mobile phone ownership is not required for participation, and a mobile phone will be provided at no cost to participants who do not have one. 

### Sample Size of Trial

Using G*power 3.1.9 (Heinrich-Heine-Universität Düsseldorf) for the ANOVA, we will set the effect size *F* at 0.35, α at .05 and the sample size at 80 (20 for each experimental condition). The calculated statistical power is 80% for detecting the 2 main effects, MES-PrEP and YaCool, and 73% for detecting their interaction. The pilot trial is not an efficacy study, and therefore is not fully powered to detect both main effects and interactions, but has a sample large enough to detect a medium to large effect size for MES-PrEP and YaCool.

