#### Phase II: Pilot MOST Design-Based Trial (R33)

We will launch a pilot trial using a full factorial design to evaluate the feasibility, acceptability, and preliminary efficacy of intervention components to increase PrEP uptake and adherence among young Thai transgender women. The trial will examine (1) the effect of each component on participants who are currently on PrEP but not adherent and participants who have not started PrEP and (2) whether the presence or absence of a component has an impact on the performance of other components. While there exist several approaches to construct a MOST trial, we will use a full factorial design given its relative simplicity and cost efficiency [48,51]. For our MOST trial, the 2 intervention components each have 2 levels, resulting in a 2^1^2^1^ full factorial with 4 experimental conditions. MOST requires a well-defined optimization criterion. We will use PrEP uptake and adherence as the measure of success. In order to build an optimized intervention for participants who are on PrEP and participants who are not on PrEP, we will enroll 80 participants who are on PrEP and 80 participants who have not started PrEP. The 80 participants who have not started PrEP will all be individuals who are at high risk and are eligible for PrEP but have not yet decided to start PrEP.

Standard PrEP counseling will be provided to all participants at the beginning of the trial and treated as a constant component in the experiment. After counseling, participants will be randomly assigned to 1 of the 4 experimental conditions (Table 1). Separate randomization for participants who are on PrEP and participants who have not started PrEP will be conducted via Qualtrics (Qualtrics XM). The primary outcome will be PrEP uptake and adherence assessed through computer-assisted self-interviewing (CASI) and dried blood spot (DBS) testing. The main effects of the intervention components and the interactions between them will be estimated using ANOVA. The goal of the R33 phase is to examine intervention strategies based on preliminary effect sizes, feasibility, and acceptability and prepare for a fully powered randomized controlled trial to evaluate the optimized intervention package.

**Table 1 table1:** Study experimental conditions.

Experimental condition (n=20 for each condition)	Standard PrEP^a^ counseling	Motivational enhancement system for PrEP	Enhanced YaCool
1	Yes	Yes	Yes
2	Yes	Yes	No
3	Yes	No	Yes
4	Yes	No	No

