### Data Analysis

#### Intervention Evaluation

We will estimate retention rates, overall and per condition, and examine differences across conditions using the chi-square test. We will assess differences in acceptability using the *t* test or the Mann-Whitney test. The minimum criteria for acceptability and feasibility will be point estimate for mean System Usability Scale score ≥50 and having at least 50% of participants respond to YaCool at least once and complete at least one MES-PrEP session [62]. Using a 2^1^2^1^ full factorial design, we will test the main effects and interactions between components with an ANOVA using effect coding (1 = “no” condition; +1 = “yes” condition) rather than dummy coding (ie, 0, 1). A participant will be classified as adherent if her tenofovir level in DBS reflects the use of TDF/FTC tablets 4 to 7 days a week over the prior 6 weeks (a level with an almost 100% preventive effect). Participants whose tenofovir levels cannot be assessed will be classified as nonadherent. The intervention effect on PrEP uptake and adherence will be further assessed using mixed-effects modeling controlling for potential confounding factors (eg, age and education) and possible baseline differences. Missing data will be handled using full information maximum likelihood estimation. Effect sizes will be estimated for the primary outcomes. All analyses will be conducted using the SAS 9.4 statistical software package (SAS Institute Inc).

Structural equation modeling will be used to examine the extent to which the targeted variables (eg, information, motivation, and self-efficacy) mediate the intervention effect. Guided by our conceptual model, we will assess the effects of intervention on the mediator and the effects of the mediator on the outcome, controlling for other mediators and confounders, and we will then estimate the proportion of the intervention effect explained. Mediation models will be tested using MPlus (Muthén & Muthén). Given the limited sample size, conclusions from the mediation analyses will be limited and treated with caution, but modeling will allow us to explore the constructs of IMB and potential predictors in preparation for a larger efficacy trial.

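### The stated power of 80% for main effects and 73% for the interaction cannot both hold in a balanced 2x2 factorial; at the stated inputs each effect has 87% power

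*Protocol article*

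**What the plan says.** The Sample Size of Trial section of the protocol article gives its tool and inputs as "Using G*power 3.1.9 (Heinrich-Heine-Universität Düsseldorf) for the ANOVA" and "we will set the effect size *F* at 0.35, α at .05 and the sample size at 80 (20 for each experimental condition"). Its result is: "The calculated statistical power is 80% for detecting the 2 main effects, MES-PrEP and YaCool, and 73% for detecting their interaction". It then says that the pilot is not an efficacy study and not fully powered for both kinds of effect, but that it "has a sample large enough to detect a medium to large effect size for MES-PrEP and YaCool".

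The design is set in the section on Phase II: "the 2 intervention components each have 2 levels, resulting in a 2^1^2^1^ full factorial with 4 experimental conditions". Table 1 there gives "Experimental condition (n=20 for each condition"). The trial enrols 80 participants on PrEP and 80 who have not started it, randomized separately, so the 80 in the power calculation is one stratum. Under Intervention Evaluation the analysis is stated as "we will test the main effects and interactions between components with an ANOVA using effect coding".

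The power statement mentions no multiplicity adjustment and no allowance for loss to follow-up.

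**The concern.** One f, one alpha and one N are given, yet two different powers are reported. In a 2x2 layout with equal cells, a main effect and the interaction are tested with the same precision and the same degrees of freedom. Nothing in the stated inputs could separate 80% from 73%.

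Two things are at stake. First, these are the only power figures in the article, and the pilot is meant to prepare a fully powered trial; the same calculation carried forward would mis-size it. Second, whether one component changes the effect of the other is one of the trial's two stated questions, and Component Selection re-evaluates the chosen components if substantial interactions appear. A figure of 73% next to 80% can suggest that interactions are almost as easy to detect as main effects. That is true only if the interaction is far larger on the outcome scale than the main effects.

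**Working it through.** **Inputs from the article.** f = 0.35, alpha = .05, N = 80, 20 per cell (Sample Size of Trial); two factors at two levels, four cells (Phase II section); ANOVA with main effects and interaction (Intervention Evaluation).

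**Degrees of freedom.** Main effect: 2 − 1 = 1. Interaction: (2 − 1)(2 − 1) = 1. Error: 80 − 4 = 76.

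**Formula.** Fixed-effects ANOVA power is the probability that a noncentral F variable with noncentrality λ = f² × N exceeds the central F critical value. Here λ = 0.35² × 80 = 0.1225 × 80 = 9.8 for every effect set at f = 0.35.

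**Attempt to reproduce the stated figures** (error df 76, λ = 9.8, alpha = .05):

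| Numerator df | Critical F | Power |
|---|---|---|
| 1 (each main effect; the interaction) | 3.967 | 87.1% |
| 2 | 3.117 | 79.0% |
| 3 (omnibus test of four cells) | 2.725 | 72.7% |

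The correct entry, 1 df, gives neither stated figure: 87.1 − 80 = 7.1 points and 87.1 − 73 = 14.1 points. A simulation of the 2x2 ANOVA (40,000 runs) gave 87.3% for a main effect and 87.2% for the interaction. The stated 73% agrees with 3 df to rounding. The stated 80% is close to 2 df (79.0%) but does not round to it. One df at alpha = .025 gives 79.9%, but that contradicts the stated .05. No single adjusted alpha yields both figures, because at any one alpha the 1-df powers are equal.

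**What f = 0.35 means for each effect.** In a balanced 2x2, f is the common size of the cell deviations due to that effect, in SD units.
- Main effect: cells lie at +f and −f, so the marginal contrast is 2f = 2 × 0.35 = 0.70 SD.
- Interaction: the difference-in-differences combines four such deviations, 4f = 4 × 0.35 = 1.40 SD.

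**Power at other sizes** (1 df, N = 80, alpha = .05):
- Interaction contrast of 0.70 SD: f = 0.70 / 4 = 0.175, λ = 0.175² × 80 = 2.45, power 34%.
- Main effect at f = 0.25 (the value usually labelled medium; the article does not define the term): λ = 0.25² × 80 = 5.0, power 60%.

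**Loss to follow-up (assumed; no rate is stated).** 1 df, f = 0.35: 83% with 72 analysed (10% loss) and 79% with 64 analysed (20% loss).

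**The case against.** The strongest reply is that the error is harmless. True power at the stated inputs exceeds both printed figures, so 80 per stratum is not too small for f = 0.35. Allocation, outcome and analysis are unaffected. The article says openly that the pilot is not fully powered for main effects and interactions together, and its claim of adequacy covers only the two components. Component Selection accepts either significance or a medium to large effect size, and it refers to substantial rather than significant interactions, so the stated power enters no decision rule. All of this stands, and it lowers the severity. It does not make the two numbers right, and the caveat does not tell the reader that an f = 0.35 interaction is twice as large a contrast as an f = 0.35 main effect.

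A reader might go further in several directions that the article does not support:
- *That wrong degrees of freedom were entered.* No numerator df is reported; the pattern is consistent with 2 and 3, but the cause is inferred.
- *That an f = 0.35 interaction is implausible, or that interactions are undetectable.* The article gives no benchmark for a plausible interaction, and the 34% applies to one chosen size.
- *That f = 0.35 equals a fixed number of percentage points.* This depends on an adherence rate that the article does not assume. Using SD = √(p(1 − p)), a 0.70 SD contrast is about 27 points at p = 18% and 35 points at p = 50%; 1.40 SD is about 54 and 70 points.
- *That attrition makes 80% too optimistic.* That rests on a loss rate that is not stated; with 64 analysed the power is still 79%.

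**Conclusion.** The point holds as a reporting error. With f = 0.35, alpha = .05 and 20 per cell, each main effect and the interaction has 87.1% power; 80% and 73% are both wrong and cannot both be true. This rests only on the article's own inputs and on equal cells.

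It does not show that the trial is too small. At f = 0.35 the stated powers err on the low side. The practical harm lies in interpretation: 73% is not a useful guide to detecting an interaction, since a contrast as large as the f = 0.35 main effect (0.70 SD) has about 34% power. The claim about medium to large effects also reaches too far down, with about 60% at f = 0.25. The severity is a correction of the text, not a change that must be made before the trial can proceed.

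**What to change.** In Sample Size of Trial:

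1. Replace both powers with 87% for each main effect and for the interaction, stating 1 numerator df, error df 76, f = 0.35, alpha = .05 and 80 participants per PrEP stratum.
2. Remove the 73% figure. State that f = 0.35 for the interaction is a 1.40 SD difference-in-differences, and that an interaction contrast as large as the f = 0.35 main effect (0.70 SD) has about 34% power.
3. Limit the claim of adequate sample size to main effects near f = 0.35, and give 60% at f = 0.25.
4. If percentage-point translations or loss scenarios are added (for example 83% with 72 analysed and 79% with 64), label the assumed adherence rate or loss as an assumption.

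The cost is wording only: no added participants and no change to design or analysis. The interaction statement becomes less favourable; the main-effect figure at f = 0.35 becomes more favourable.

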**Methods:**

We will utilize a multiphase optimization strategy (MOST) to identify the most effective intervention component or combination of components to improve PrEP usage in Thai transgender women. The study includes two phases: phase I (R21) includes qualitative interviews with key stakeholders to explore barriers and facilitators of PrEP usage through thematic analysis to inform intervention adaptation. Following this, we will adapt and beta-test MES-PrEP and Enhanced YaCool for functionality and feasibility using a community advisory board of HIV-negative Thai transgender women. In phase II (R33), we will conduct a MOST design-based trial to evaluate the feasibility, acceptability, and preliminary efficacy of MES-PrEP and Enhanced YaCool. Eighty HIV-negative participants who are currently taking PrEP and 80 participants who are not will be randomized to four conditions: (1) standard PrEP counseling (the control condition); (2) MES-PrEP and standard PrEP counseling; (3) Enhanced YaCool and standard PrEP counseling; and (4) MES-PrEP, Enhanced YaCool, and standard PrEP counseling. Feasibility and acceptability of the intervention will be assessed through usage patterns and the System Usability Scale. Preliminary impact will be assessed by evaluating the proportion of participants who initiate PrEP and their level of adherence to PrEP. Assessments will be at baseline and 1, 3, 6, 9, and 12 months postintervention. Biomarkers of adherence to PrEP, HIV, and other sexually transmitted infections will be collected.

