Pre-exposure prophylaxis (PrEP) is highly effective when taken as prescribed, and daily use has been shown to reduce the risk of HIV infection by 92% [21], but PrEP uptake among transgender women worldwide is low. Studies have shown that this is primarily due to lack of awareness, rather than lack of willingness to use PrEP [22,23]. Further, adherence among transgender women has been found to be only 18%, compared to 52% among men who have sex with men [24], yet PrEP research has primarily focused on men who have sex with men [25]. In the Princess PrEP program, the largest PrEP program in Thailand, 232 transgender women began using PrEP in 2019, but only 43 were using it at month 3, reiterating the challenges of adherence among this population [26]. Common facilitators of PrEP uptake among transgender women include a high perception of HIV risk, accurate knowledge of PrEP, and access to support services [27,28]. Barriers to PrEP uptake and adherence include concerns about side effects, especially interactions with gender-affirming hormone therapy, a low perception of HIV risk, the stigma of HIV, health system inaccessibility, exclusion of transgender women from advertising, and lack of research [27-29], especially in low- and middle-income countries. Effective and sustainable behavior-change interventions are needed to promote PrEP uptake and adherence in high-risk populations like transgender women in Thailand and end the global HIV epidemic.

mHealth may offer a powerful tool to promote behavior change, particularly when based on evidence-based interventions, such as motivational interviewing (MI) [30,31]. Mobile apps that offer feedback and self-monitoring of health have been associated with improved health outcomes [32]. There is also evidence that text message reminders can improve adherence to prevention and treatment across many clinical conditions, especially among emerging adults [18,33]. Text messaging and mobile apps may have great potential to promote health self-management and behavior change in young transgender women, but are currently underutilized [7]. Mobile interventions are useful among emerging adults due to nearly universal technology use [34,35], and appear to increase PrEP adherence among young people at risk for HIV [36,37]. Still, very few technology-based interventions have targeted transgender women.

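### The stated power (80% and 73% at f = 0.35) does not match the planned 1-df tests, and names neither the outcome nor the proportions it refers to, although uptake and DBS adherence are yes/no

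*Protocol article*

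**What the plan says.** In Sample Size of Trial, the power calculation uses G*Power for an ANOVA with f = 0.35, α = .05 and 80 participants, 20 per condition. "The calculated statistical power is 80% for detecting the 2 main effects, MES-PrEP and YaCool, and 73% for detecting their interaction". The section describes the pilot as not fully powered for both main effects and interaction, but says it "has a sample large enough to detect a medium to large effect size for MES-PrEP and YaCool". It names no outcome, reference rate or target difference.

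The outcomes are described elsewhere. The abstract's Methods paragraph promises "evaluating the proportion of participants who initiate PrEP and their level of adherence to PrEP". Under Intervention Evaluation, "A participant will be classified as adherent if her tenofovir level in DBS reflects the use of TDF/FTC tablets 4 to 7 days a week", and a participant whose level cannot be assessed counts as nonadherent, so this outcome is yes/no. The same section tests main effects and interaction in a 2×2 ANOVA with effect coding. Data Collection Tools and Procedures also lists two self-reported adherence measures that are close to continuous: a visual analog scale and a 4-week percentage taken.

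The two strata are randomised separately, and Table 1 gives "Experimental condition (n=20 for each condition"). The only adherence rate of use as a reference is in the Background: "adherence among transgender women has been found to be only 18" per cent.

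**The concern.** Cohen's f is the spread of group means divided by a common within-group standard deviation. For a proportion, that standard deviation depends on the rate itself, so an f without rates does not say what difference the trial can see. It also matters which scale f is on. An effect of 0.35 on the measured drug level becomes smaller, in f units, once the level is cut at a threshold. An effect of 0.35 on the 0/1 outcome does not shrink, but it is a large difference in percentage points.

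Separately, with two levels per component and effect coding, each main effect and the interaction is a single contrast. At the same f all three must have the same power, so printing 80% and 73% for them shows that something in the calculation differs from the planned tests.

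Under Component Selection, a component is chosen provisionally if it is significant or shows a medium to large effect. The result feeds the larger trial, so readers need to know which differences in uptake and adherence this pilot could miss.

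**Working it through.** **Inputs from the protocol article.** f = 0.35, α = .05 and N = 80 (Sample Size of Trial); 20 per cell, so 40 vs 40 for each component in a stratum (Table 1); 1-df effect-coded contrasts (Intervention Evaluation). **Assumed:** the reference rate, because no design rate is given.

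**1. The plan's own figures.** Noncentral F with λ = f²N = 0.1225 × 80 = 9.8 and 80 − 4 = 76 denominator df:

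| Numerator df | Critical F | Power | Stated |
|---|---|---|---|
| 1 | 3.97 | 87.1% | – |
| 2 | 3.12 | 79.0% | 80% (main effects) |
| 3 | 2.72 | 72.7% | 73% (interaction) |

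The stated figures return, to within about a point, only with 2 and 3 numerator df. One df at α = .025 gives 79.9%, but that contradicts the stated α and does not explain the 73%. The planned 1-df tests have 87.1% for a main effect and the same for an interaction of f = 0.35. An interaction of that size is large: the effect-coded coefficient is 0.35 SD, so one component's effect must differ by 4 × 0.35 = 1.4 SD between the two levels of the other.

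**2. f = 0.35 read on the 0/1 outcome.** For two equal groups, f = (p₁ − p₀)/2 ÷ √{[p₀(1−p₀) + p₁(1−p₁)]/2}. Setting f = 0.35 gives:

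| p₀ (assumed) | p₁ | Difference (points) |
|---|---|---|
| 10% | 38.3% | 28 |
| 18% | 49.2% | 31 |
| 30% | 63.0% | 33 |
| 50% | 81.4% | 31 |

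Power with 40 vs 40 is about 85% (pooled z) to 87% (exact chi-square).

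**3. f = 0.35 read on the drug level, then cut to yes/no.** For a two-level factor d = 2f = 0.70. With a normal underlying level, p₁ = Φ(Φ⁻¹(p₀) + 0.70). At p₀ = 18%, p₁ = Φ(−0.915 + 0.70) = 41.5%. Pooled-z power is

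Φ{[Δ − 1.96√(2p̄(1−p̄)/40)] ÷ √([p₀(1−p₀) + p₁(1−p₁)]/40)} = Φ{(0.235 − 0.200)/0.0988} ≈ 64%.

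The exact chi-square test gives 63.9%, and a simulated 2×2 ANOVA on 0/1 data gives 64.7%. Over other assumed rates (pooled z):

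| p₀ | 5% | 10% | 18% | 30% | 36% | 50% | 70% |
|---|---|---|---|---|---|---|---|
| Power | 41% | 54% | 64% | 69% | 69% | 67% | 56% |

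The highest value by any of these three methods is about 72%, near a median split. The like-for-like comparison is with 87%, not with the printed 80%.

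**4. What 40 vs 40 can see on the proportion scale.** About 80% power needs 10% vs 36%, 18% vs 47% or 30% vs 61%. For 18% vs 47%, (0.290 − 0.205)/0.0996 = 0.85, and Φ(0.85) = 80%. In Cohen's h, 18% vs 47% is 2(asin√0.47 − asin√0.18) = 0.63. A medium effect, h ≈ 0.5 (18% vs 40%), has (0.220 − 0.199)/0.0984 = 0.215, and Φ(0.215) = 59%.

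**The case against.** The strongest reply is that nothing ties f = 0.35 to the drug level. Read on the 0/1 outcome, power is 85-87%, which is above the stated 80%, so a yes/no outcome does not by itself make the printed figure too high. This stands. A reader might infer that the trial has about 64% power instead of 80%, but the documents do not support that. The 64% needs f to be on the drug level, a normal underlying distribution and an 18% reference rate. That rate is a literature figure in the Background. It describes neither stratum, since PrEP users enter because they take few pills and the others have not started.

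A reader might also infer that the medium to large claim is false. It is not refuted: 18% vs 47% is h = 0.63, between the conventional 0.5 and 0.8. Only the medium end falls short.

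Three further points stand. Not every outcome is yes/no, because the two self-reported measures are near-continuous, so the abstract's mention of adherence level is not wholly abandoned. Dichotomisation loss does not apply to uptake, which is an event with no measured level behind it. The threshold has a stated clinical rationale, and the pilot disclaims full power, with provisional selection that also weighs cost, feasibility and scalability.

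None of this explains printed figures that do not belong to the planned tests, or a detectability claim with no outcome or rates attached.

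**Conclusion.** The point holds as a fault in the power statement, not as proof that the trial is too small. The 80% and 73% fit 2- and 3-df tests. The planned 1-df tests have about 87% at f = 0.35 on a continuous outcome and about 85-87% on the 0/1 scale, so on either of these readings the printed figures are too low. On the third reading, an effect on the tenofovir level cut to yes/no, they are too high: about 41-72% for a main effect over assumed reference rates of 5-70%. The stated 80% matches none of the three.

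The practical limit is that, on yes/no outcomes, the trial reliably sees only differences of roughly 26-31 percentage points over assumed reference rates of 10-30%, which the article does not say. All the proportion-scale figures rest on assumed rates and on complete data for 40 per component level. ANOVA on 0/1 data is not itself the problem here: simulated type I error was 0.049-0.055 at rates of 10-30%, and a logistic model would change little.

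**What to change.** Restate the power for the 1-df tests on the outcome analysed, separately for uptake and DBS adherence, with the reference rate marked as an assumption. For example: with 40 per component level, about 80% power for 18% vs 47%, and about 59% for 18% vs 40%. Replace the 80% and 73%, and give the interaction on the same scale as a difference between two differences. Report risk differences with confidence intervals for uptake and adherence.

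In the PrEP-user stratum, keep the protective threshold as planned. Add a factorial analysis of the DBS level, on the log scale or in ordered dosing categories if only those are reported, adjusted for its baseline value, to inform component selection.

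This needs wording and one added analysis, with no more participants. DBS is already planned, although the adjusted analysis needs a baseline value for each PrEP user. The cost is a pre-specified rule for values below the limit and for samples that cannot be assessed. A mean level is also less directly clinical than the threshold, which is why it should be added and not substituted.
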